### Appendix 9: Survey about Risk Assessment and Shared Decision Making (for those that decline a CT scan)

“Survey about your experiences of the lung cancer screening study”

Tēnā koe

As part of our study we are checking your experiences of the lung cancer screening study. Please complete this survey to help us improve the way lung screening is offered in the future. This survey is voluntary.

| 1. Was the study explained to you before your risk assessment? | Yes 🞏 No 🞏 |
| --- | --- |
| 1. Was the information given to you about the study informative and helpful? | Yes 🞏 No 🞏 |
| 1. Was the risk assessment clearly explained to you before it started? |  |
| 1. What would have improved the information you received? (E.g. pictures or diagrams, less jargon) |  |
| 1. What was your first reaction when you were invited to take part in the study? (for example, were you curious/ worried / confused / excited?) |  |
| 1. How did you feel when the Assessment showed you had a higher risk of lung cancer and were eligible for a CT scan? |  |
| 1. Were you offered any health related information such as information on smoking?   If not, would you like to be referred to some of our services? | Yes 🞏 No 🞏  Yes 🞏 No 🞏 |
| 1. Do you remember the study nurse explaining the risks and benefits of lung cancer screening to you when you were deciding whether to have a CT scan or not? | Yes 🞏 No 🞏 |
| 1. Did you have this discussion in person/over the phone/ over video call? | In person 🞏 By phone 🞏  By video 🞏 |
| 1. If over the phone or video call, did you find this method as effective as an in-person appointment? | Yes 🞏 No 🞏 |
| 1. Did this discussion help you to make your decision to take part in lung screening? | Yes 🞏 No 🞏 |
| 1. Did you feel comfortable talking with the nurse or doctor? | Yes 🞏 No 🞏 |
| 1. Did you feel you were fully informed of the risks and benefits of lung cancer screening? | Yes 🞏 No 🞏 |
| 1. How did you feel after you made your decision about the CT scan? |  |
| 1. What went well during your discussion with the nurse when you were making a decision about whether or not to have a CT scan? |  |
| 1. Was there anything during your discussions that didn’t go well? |  |
| 1. What can we do to make the decision making process better? |  |
| 1. Do you have any other comments on what worked well or could be improved about this process? |  |

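### One Yes/No item in the survey for people who decline the CT scan (Appendix 9) presupposes a decision to take part, so decliners' answers to that item are ambiguous

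*Protocol*

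**What the plan says.** By its title, Appendix 9 is for people who decline a CT scan. It has 18 rows, and the eleventh is a Yes/No item: "Did this discussion help you to make your decision to take part in lung screening". Appendix 10, for people who have the scan, carries the same question word for word.

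Elsewhere Appendix 9 is neutral about which way the person decided. Three rows earlier it asks whether the respondent remembers the nurse "explaining the risks and benefits of lung cancer screening to you when you were deciding whether to have a CT scan or not". Later it asks "How did you feel after you made your decision about the CT scan", and what went well in the discussion "when you were making a decision about whether or not to have a CT scan".

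Experience and acceptability of shared decision making is a listed secondary outcome (Outcomes and Significance, Secondary outcomes). The section on secondary research questions places it among the qualitative questions. It says these will be addressed through the appendix questionnaires together with focus groups, interviews and primary care provider feedback, and that the views of non-participants will be recorded. The section on shared decision making gives the purpose of the discussion as an informed choice about going ahead or not.

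**The concern.** Declining is a legitimate result of a good discussion, so a decliner should be able to say whether the discussion helped. This is the only closed item that asks so directly, and it is worded for the opposite decision. It offers only Yes or No, with no comment box or third option that would separate the possible meanings. No later analysis can recover what a respondent meant.

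What is at stake is one piece of evidence on a descriptive secondary outcome, from the group whose view of the process is of particular interest: people who were offered the scan and chose against it. The wording is fixed in the protocol's own appendix, so it is not a matter left to a statistical analysis plan.

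**Working it through.** The protocol states no figure for this item, so the check compares the forms and counts what is affected.

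**1. Possible meanings of each answer**

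| Answer | Appendix 10 (had the scan) | Appendix 9 (declined) |
| --- | --- | --- |
| Yes | The discussion helped me decide to go ahead | It helped me decide to decline; or it helped with taking part in something else, such as the risk assessment |
| No | The discussion did not help | It did not help; or the question does not apply because I did not take part |

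In Appendix 10 each answer has one natural meaning. In Appendix 9 each has at least two, so equal percentages of Yes on the two forms would not measure the same thing.

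**2. How much of Appendix 9 is affected**

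Rows 8 to 17 concern the discussion or the decision, which makes ten items.

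- Closed (six): recall of the explanation; mode of discussion; whether phone or video was as effective; whether the discussion helped; "Did you feel comfortable talking with the nurse or doctor"; and "Did you feel you were fully informed of the risks and benefits of lung cancer screening".
- Open (four): feeling after the decision; what went well; what did not go well; and "What can we do to make the decision making process better".

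Only the item on whether the discussion helped presupposes taking part. That is 1 of 10 overall and 1 of the 6 closed items. The remaining 10 − 1 = 9 can be answered by a decliner as they stand.

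**3. How many people could meet the item**

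Inputs from the Synopsis, expected sample size: 1134 eligible for a scan; 500 to 550 consenting to or having one (the Synopsis uses the same range for both).

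- 1134 − 550 = 584, and 584/1134 = 51.5%
- 1134 − 500 = 634, and 634/1134 = 55.9%

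These are ceilings. They count everyone eligible who is not scanned, including people who agreed but did not attend and people who never completed shared decision making. The protocol treats deciding to proceed and attending as separate steps. The survey is also voluntary, and no response rate is given.

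**The case against.** The strongest reply is that this is a slip in one survey row and that little depends on it. Much of that stands. A reader might infer that the decliners' answers on shared decision making as a whole cannot be interpreted. The documents do not support this: nine of the ten relevant items are neutral, and focus groups and interviews feed the same outcome. The primary outcome, and the secondary outcome on the proportion who proceed after shared decision making, rest on recorded behaviour and not on this survey.

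A reader might also infer that decliners' answers are biased towards the discussion not having helped. That is not shown. The neutral item three rows earlier could lead a decliner to read this one as asking about the decision they did make, and to answer Yes. The ambiguity runs both ways. Nor does the protocol plan a comparison of decliners with scan-takers on this item, so no stated analysis is distorted.

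Identical text in the two appendices suggests a line that was not adapted, but the documents do not show where it came from. Appendix 10's version fits its own respondents.

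What the reply does not remove is the ambiguity itself. The item is in a data-collection form for a stated secondary outcome, and its answers cannot be repaired once collected.

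**Conclusion.** The point holds for one item only. In Appendix 9, the Yes/No question on whether the discussion helped presupposes a decision that its respondents did not make. Their answers to it are ambiguous and not comparable with those to the same question in Appendix 10. This is a minor fault, worth correcting because it changes what the form measures and costs almost nothing to remove.

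The number of people who could be affected is at most 584 to 634, and in practice fewer. That ceiling rests on the Synopsis expectations of 1134 eligible and 500 to 550 scanned. It would move if those numbers are adjusted to reach the scan target, as the Synopsis allows. It should not be read as a count of responding decliners.

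**What to change.** Reword the Appendix 9 item in the neutral form used elsewhere in that survey, for example: *Did this discussion help you decide whether or not to have a CT scan?* If the two groups' answers are to be set side by side, preferably use the same sentence in Appendix 10. Otherwise Appendix 10 can stay as it is.

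If any decliners have already answered the existing wording, report their responses to this item separately and do not pool them with later ones.

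The cost is one line in one form, or in two if Appendix 10 is aligned. Sample size, procedures and the primary analysis do not change.

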### Appendix 10: Survey about Shared Decision Making and CT scan (for all participants having a CT scan)

“Survey about your experiences of the lung cancer screening study”

Tēnā koe

Thank you for taking part in Te Oranga Pūkahukahu Lung Health Check. We have a few questions about your recent experiences with us, which we hope will improve our service.

| 1. Was the study explained to you before your risk assessment? | Yes 🞏 No 🞏 |
| --- | --- |
| 1. Was the information given to you about the study informative and helpful? | Yes 🞏 No 🞏 |
| 1. Was the risk assessment clearly explained to you before it started? |  |
| 1. What would have improved the information you received? (E.g. pictures or diagrams, less jargon) |  |
| 1. What was your first reaction when you were invited to take part in the study? (for example, were you curious/ worried / confused / excited?) |  |
| 1. How did you feel when the Assessment showed you had a higher risk of lung cancer and were eligible for a CT scan? |  |
| 1. Were you offered any health related information such as information on smoking?   If not, would you like to be referred to some of our services? | Yes 🞏 No 🞏  Yes 🞏 No 🞏 |
| 1. Do you remember the study nurse explaining the risks and benefits of lung cancer screening to you when you were deciding whether to have a CT scan or not? | Yes 🞏 No 🞏 |
| 1. Did you have this discussion in person/over the phone/ over video call? | In person 🞏 By phone 🞏  By video 🞏 |
| 1. If over the phone or video call, did you find this method as effective as an in-person appointment? | Yes 🞏 No 🞏 |
| 1. Did this discussion help you to make your decision to take part in lung screening? | Yes 🞏 No 🞏 |
| 1. Did you feel comfortable talking with the nurse or doctor? | Yes 🞏 No 🞏 |
| 1. Did you feel you were fully informed of the risks and benefits of lung cancer screening? | Yes 🞏 No 🞏 |
| 1. How did you feel after you made your decision about the CT scan? |  |
| 1. What went well during your discussion with the nurse when you were making a decision about whether or not to have a CT scan? |  |
| 1. Was there anything during your discussions that didn’t go well? |  |
| 1. What can we do to make the decision making process better? |  |

Having a CT scan

1. How was your experience of getting a CT scan?

|  |  |  |  |  |
| --- | --- | --- | --- | --- |
| I was very happy with the way it went | It was OK | Neutral /  Don’t know | It wasn’t great | I was unhappy with the way it went |

Please add any comments you would like to make:

1. Would you recommend having a CT scan for lung screening to other people? Yes/No
   Please can you explain your answer:
2. Did the information you were given prepare you what happened during the CT scan?

|  |  |  |  |  |
| --- | --- | --- | --- | --- |
| Yes I was very prepared | Prepared | Neutral /  Don’t know | Slightly unprepared | No I was very unprepared |

Please add any comments you would like to make:

1. What can we do to make the CT scan process better?

Please give us your suggestions for improvements:

1. Is there anything else you want to say?:

### Appendix 11: Survey after a CT scan (selected participants)

Tēnā koe

As part of our study we are checking your experience of the CT scan for lung screening. Please complete this survey to help us improve the way lung screening is offered in the future. This survey is voluntary.

| 1. Are you happy with the information given to you to prepare for the CT scan? | Yes 🞏 No 🞏 |
| --- | --- |
| 1. Did you feel any worry or anxiety about having a CT scan? | Yes 🞏 No 🞏 |
| 1. If yes, what was the cause of your worry or anxiety? | I was afraid of the results 🞏  I was uncomfortable having a CT scan 🞏  I tend to be worried or anxious about medical tests 🞏  Other 🞏  Please comment: |
| 1. Did the study staff help you with managing your worry or anxiety? | Yes 🞏 No 🞏 |
| 1. Are you satisfied with the quality of care you received? | Yes 🞏 No 🞏 |
| 1. How was your experience of having a CT scan? | Fine 🞏 Better than expected 🞏  Worse than expected 🞏 |
| 1. Did you feel safe going into the CT scan? | Yes 🞏 No 🞏 |
| 1. Did anything happen during the CT scan that would put you off consenting to a CT scan in the future? | Please comment: |
| 1. Were you told when you would get your CT scan results? | Yes 🞏 No 🞏 |
| 1. Did you get your CT scan results on time? | Yes 🞏 No 🞏 |
| 1. Is there anything that could have prevented you from attending the CT scan? (such as travel costs, family commitments etc.) | Please comment: |
| 1. Did you get enough information about your CT scan results? | Yes 🞏 No 🞏 |
| 1. Was the explanation of your CT scan result easy to understand? | Yes 🞏 No 🞏 |
| 1. Do you know what your next steps are? (E.g. doctors appointment, follow up scan in one year etc.)? | Yes 🞏 No 🞏 |
| 1. Would you do lung cancer screening again in the future if it was available ? | Yes 🞏 No 🞏 |
| 1. Have you made any health changes since taking part in this study? | Yes 🞏 No 🞏 |
| 1. Would you recommend lung cancer screening to your whānau and friends? | Yes 🞏 No 🞏 |

### Appendix 12: Whānau Tautoko Survey

Tēnā koe,

Thank you for agreeing to take part in this survey and for supporting your whānau member through their lung screening journey.

This survey is for whānau tautoko (support people) to share your whakaaro (thoughts) to support the kaupapa of the lung screening study.

By answering these questions, you are consenting to the research team including this information in an analysis of how well the lung screening research programme is working. All answers are anonymous and you will not be able to be identified.

You do not have to participate in this questionnaire if you don’t want to, and if you say no, this will in no way affect the care your whānau member receives.

Please make sure you are completing the correct survey: this is for **whānau tautoko**.

1. Was your whānau member treated with respect during the study?
2. What can we do to improve the way we support people who are going through lung screening*?*
3. What can we do to help whānau who are supporting someone going through lung screening?
4. Was the information we gave to your whānau member, and to the whānau, too much / just right / not enough?
5. Was the assessment process easy to understand?
6. Was the shared decision making process easy to understand?
7. Did the system to book the appointment work well for your whānau?
8. Did the appointment times that were offered to your whānau work? If no, why not?
9. Is there anything you would like us to know about your whānau experience with lung cancer screening?
10. What is your gender? Male Female Gender diverse Prefer not to answer
11. What age are you? 16-19 | 20-29 | 30-39 | 40-49 | 50-59 | 60-69 | 70-79 | 80+
12. Do you identify as (please tick all that apply)
    New Zealand European|Māori | Samoan| Cook Islands Māori |Tongan |Niuean |Chinese| Indian| Other
13. If you identify as Māori, which iwi do you whakapapa/connect to? (Can be more than 1)
    Iwi:

### Appendix 13: Hua Oranga Questionnaire

[figure not shown]

[figure not shown]

### Appendix 14: Survey after COPD Assessment (all COPD participants)

Tēnā koe

Thank you for taking part in an assessment for COPD. We would like to know how you found this. Please complete this survey – this will help us improve the way we do COPD assessments in the future. This survey is voluntary. (Note – this interview will be conducted with the study nurse, immediately after the assessment).

| 1. Was the COPD assessment explained to you in a way that you understood? | Yes 🞏 No 🞏 |
| --- | --- |
| 1. *If no:* How could it have been better? Please comment: | |
| 1. Is there any other information that would have been helpful for you? | Yes 🞏 No 🞏 |
| 1. *If yes:* What would that have been? Please comment: | |
| 1. Is there anything that could have prevented you from attending the COPD assessment (such as travel costs, family commitments, etc…). Please comment: | |
| 1. What was helpful for you about the COPD assessment? Please comment: | |
| 1. What else might have been helpful? Please comment: | |
| 1. Did you get enough information about the results of your COPD assessment? | Yes 🞏 No 🞏 |
| 1. *If no:* Please comment: | |
| 1. Overall, how did you feel about your experience of getting a CODP assessment as part of your lung health check? Please comment:  \|  \|  \|  \|  \|  \| \| --- \| --- \| --- \| --- \| --- \| \| I was very happy with the way it went \| It was OK \| Neutral /  Don’t know \| It wasn’t great \| I was unhappy with the way it went \|   Please add any comments you would like to make: | |
| 1. Is there anything else you can tell us about your experience of being assessed for COPD?   Please comment: | |

### Appendix 15: Qualitative interview after COPD assessment

**Interview Schedule**

Meet and greet/whakawhānaungatanga/Karakia

Discuss purpose and reminder re: dates and process they underwent (assessment and screening)

Note: have on hand pictures of tools used as a reminder – playing on the assumption participants may have had multiple medical appointments pre and post timeframe.

Go over information sheet (will be sent prior) and a copy carried with interviewer.

Consent signed (2 x copies – one to be left with participant).

Interview: What was participant and or whānau experience undergoing the LCS and COPD assessment?

1. Tell me about your experience in relation to LCS and COPD assessment
   Go through each step: appointment: being contacted (method), pre and post attendance, understanding process, information, outcome, next steps, did you have to take time off work, what motivated you to participate?
   1. What worked well, what did they like, what could have been better/more helpful?
   2. What did not work well for them, what were some of the challenges or difficulties through each step? (e.g. understanding, location, parking etc)
   3. Do you have any feedback on the screening/assessment (if necessary, go through the process including: arrival, workforce, attitude, way you treated, process, equipment, feelings and information post screening)?
   4. If you knew someone else had the same appointment, what would you tell them to expect or what would you say that might be helpful or make things easier for them?
2. Was it helpful having both the COPD assessment and screening at the same appointment? If so or not, can you tell me why? Is that something that would be good to do in the future for others?
3. Can you tell me how you felt after the assessment?
   1. How were findings given, support offered or present, next steps and information) is there anything that could have been done better or differently in relation to being told the outcome/findings
4. Tell me what it was like for you to be part of the shared decision-making COPD results management process (lay terms)
   1. Reminding them of what some of the decisions and results may have been and what the next steps were...
5. Do you know if information goes to your GP? Query the experience of provision of information to their GP
   1. Are you happy with information that goes to your GP, are you comfortable asking about information, do you understand what goes to your GP?
6. Is there anything they want to ask of us, their healthcare professional or the research team, or to add?

Closing / Karakia

### Appendix 16: Survey after Biomarker Assessment (all Biomarker participants)

Tēnā koe

Thank you for taking part in the biomarker assessment for lung cancer screening. We would like to know how you found this. Please complete this survey – this will help us improve the way we do biomarker assessments in the future. This survey is voluntary. (Note – this interview will be conducted with the study nurse, immediately after the assessment).

| 1. Was the biomarker assessment explained to you in a way that you understood? | Yes 🞏 No 🞏 |
| --- | --- |
| 1. *If no:* How could it have been better? Please comment: | |
| 1. Is there any other information that would have been helpful for you? | Yes 🞏 No 🞏 |
| 1. *If yes:* What would that have been? Please comment: | |
| 1. Is there anything that could have prevented you from attending the biomarker assessment appointment (such as travel costs, family commitments, etc…). Please comment: | |
| 1. What was helpful for you about the biomarker assessment? Please comment: | |
| 1. What else might have been helpful? Please comment: | |
| 1. Is there anything else you can tell us about your experience today?   Please comment: | |
| 1. Overall, how did you feel about your experience of getting a biomarker test as part of your lung health check? Please comment:  \|  \|  \|  \|  \|  \| \| --- \| --- \| --- \| --- \| --- \| \| I was very happy with the way it went \| It was OK \| Neutral /  Don’t know \| It wasn’t great \| I was unhappy with the way it went \|   Please add any comments you would like to make: | |

### Appendix 17: Training evaluation survey

Tēnā koe,

In your role as a provider of support to the participants of the Lung Screening Study, you recieved some training about the study, about lung cancer and about how to talk to participants with positive scans and concerning results. We would like to invite you to complete a short questionnaire to provide feedback on this training.

Your individual feedback will not be identifiable. Any report will only include summarised findings, meaning anyone reading the report will not be able to tell who took part in the survey or who said what,

Do I have to take part?

Your participation is voluntary- you do not have to participate if you don't want to. You can also decline to answer any specific questions. Whether or not you agree to take part will have no impact on your employment or on any other aspect of your work.

By answering these questions, you are consenting to the research team including this information in an analysis of how well the lung screening research programme is working. All answers are anonymous and you will not be able to be identified.

| **1)** | **Please indicate your role:** | ****  Practice Nurse  GP  Other  [reset](javascript:;) |
| --- | --- | --- |
| **2)** | Please rate your knowledge of the following **before** you received the study training:  **Lung cancer signs and symptoms** | \| \| 1- very poor \| 5 \| 9- very good \| \| --- \| --- \| --- \| \| \| \| \| --- \| --- \| --- \| --- \| --- \| --- \| \|  \|  \|  \| \| Change the slider above to set a response \| \| \|   [reset](javascript:;) |
| **3)** | **Appropriate referral pathways for people diagnosed with a lung nodule:** | \| \| 1- Very poor \| 5 \| 9- Very good \| \| --- \| --- \| --- \| \| \| \| \| --- \| --- \| --- \| --- \| --- \| --- \| \|  \|  \|  \| \| Change the slider above to set a response \| \| \|   [reset](javascript:;) |
| **4)** | **Before this study, how confident were you dealing with a person with a suspected lung cancer?** | ****No Confidence Uncertain Confident Very Confident  [reset](javascript:;) |
| **5)** | Please rate your knowledge of the following **after**you received the study training:  **Lung cancer signs and symptoms** | \| \| 1- very poor \| 5 \| 9- very good \| \| --- \| --- \| --- \| \| \| \| \| --- \| --- \| --- \| --- \| --- \| --- \| \|  \|  \|  \| \| Change the slider above to set a response \| \| \|   [reset](javascript:;) |
| **6)** | **Appropriate referral pathways for people diagnosed with a lung nodule:** | \| \| 1- Very poor \| 5 \| 9- Very good \| \| --- \| --- \| --- \| \| \| \| \| --- \| --- \| --- \| --- \| --- \| --- \| \|  \|  \|  \| \| Change the slider above to set a response \| \| \|   [reset](javascript:;) |
| **7)** | **After this study, how confident are you dealing with a person with a suspected lung cancer?** | ****No Confidence Uncertain Confident Very Confident  [reset](javascript:;) |
| **8)** | **Please indicate how well you think the training prepared you to support participants of the Lung Screening Study:** | \| \| 1- Very poorly \| 5 \| 9- Very well \| \| --- \| --- \| --- \| \| \| \| \| --- \| --- \| --- \| --- \| --- \| --- \| \|  \|  \|  \| \| Change the slider above to set a response \| \| \|   [reset](javascript:;) |
| **9)** | **Specifically, please indicate how well you think the Shared Decision Making materials prepared you to support participants of the Lung Screening Study:** | \| \| 1- Very poorly \| 5 \| 9- Very well \| \| --- \| --- \| --- \| \| \| \| \| --- \| --- \| --- \| --- \| --- \| --- \| \|  \|  \|  \| \| Change the slider above to set a response \| \| \|   [reset](javascript:;) |
| **10)** | **Please indicate how helpful you found the Shared Decision Making process when explaining the study to potential participants:** | ****Not at all helpful Somewhat helpful Extremely helpful  [reset](javascript:;) |
| **11)** | **Do you have any comments that you would like to make about the training received?** | **** |

